#### Health service utilization

Several key secondary outcomes of the TASA study are linked to whether the study intervention can reduce or smooth health service utilization. Previously identified health service impacts of synchronized social assistance include ED, EDMH or SUH admissions [7, 11–13, 19, 57]; discharges against medical advice directly prior to cheque issue [7, 9, 12]; health service access barriers linked to elevated demand [6]; and interruptions to ongoing medical care [9, 22]. In support of these assessments the study instrument collects past six months (baseline) and past 2 weeks (baseline and follow-up) information on which health services were accessed, whether participants attempted but were unable to access a service, the timing and reason for encountering service access barriers and whether participants missed medical appointments around cheque issue. We additionally collect information on whether, if hospitalized, participants left hospital against medical advice, as well as the reasons for and timing of their departure.

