### Data linkages

To verify participant self-report wherever possible, and supplement data for the assessment of cheque issue-related costs incurred by institutions that provide social, health, financial and security (i.e., policing) services to PWUD and their communities, we will obtain third party service provision and administrative records from external databases on all participants. Participant records will be requested from hospitals, health service providers, the provincial prescription medication database, Provincial Ministry of Social Development and Social Innovation, study partner credit union, and police and criminal justice databases. Records will be requested for a 30-month period beginning 1 year before the beginning of active study participation through to 1 year after following the completion of active study participation in order to assess the impact of study involvement on access to medical and social services over time. Data linkages will be established through participant names, birth dates and participants’ personal health number, a unique and persistent identifier issued for medical billing and tracking purposes to all residents of British Columbia. Data will be de-identified to protect participant confidentiality.

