### Data analysis

#### Quantitative analyses

At the conclusion of the trial, the primary and secondary endpoints will be assessed via intention-to-treat analyses [67], including all patients randomized regardless of compliance with the intervention protocol. Sub-analyses will include a modified intention-to-treat analysis that will use all participants with at least one follow-up [67, 68]. First, we will compile descriptive characteristics of the sample, assessing for systematic differences in key characteristics across study arms using the Chi-Square test for binary variables and the Mann-Whitney *U* test for continuous variables. The primary outcome of interest will be derived from TLFB information as a repeated binary variable (intensified drug use on the 3 days beginning with government cheque issue day vs. not) and will be quantified as the proportion of individuals TASA participants reporting increased drug use during this period at each government cheque issue. This outcome, and other secondary outcomes similarly quantified will be examined using pooled generalized linear mixed effects models, with binomial distribution and logit link specified to produce unadjusted and adjusted odds ratios and 95 % confidence intervals. Other secondary outcomes of interest, quantified as counts of the number of occurrences over the course of the observation period (e.g., hospital ED admissions), will be examined using generalized linear mixed-effects model, with a Poisson distribution and a log link specified for count data with corrections for overdispersion, including a Vuong test for overdispersion and, where indicated, the use of a negative binomial model [69]. All analyses will include binary indicators of study arm allocation to assess for systematic differences in primary and secondary outcomes of interest across study arms. Multivariate analyses will be adjusted for: (1) binary indicators of the type of income assistance the participant receives; (2) an indicator variable for whether the individual changed their financial service provider to Pigeon Park Savings (PPS) at the start of the study to control for the effect of becoming a PPS client; (3) socio-demographic characteristics, including gender, ethnicity and age; indicators of addiction treatment enrollment and DTES residency, and (4) a categorical variable for the number of days between government cheque issue and their study visit to account for differences in recall reliability. As is common in RCT analyses [70, 71], missing assessments of intensified drug use will be treated as positive and tested for sensitivity to this assumption [72, 73]. Additional sensitivity analyses will include: (1) a modified intention-to-treat analysis using all participants with at least one follow-up assessment [74]; and (2) per-protocol analyses of participants who maintain enrollment in the intervention [75, 76].

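### The adjusted models include no pre-randomisation level of the outcome, although a year of pre-study records is requested, so some precision is left unused on the linked-record count outcomes

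*Protocol article*

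**What the plan says.** Under Quantitative analyses, the protocol article sends outcomes counted over the observation period, with emergency department admissions as the example, to a Poisson mixed model, or to a negative binomial model where overdispersion is found. Unadjusted and adjusted estimates are named for the binary models, and a covariate list follows for the multivariate analyses in general:

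- "Multivariate analyses will be adjusted for: (1) binary indicators of the type of income assistance the participant receives"
- "an indicator variable for whether the individual changed their financial service provider to Pigeon Park Savings (PPS) at the start of the study"
- "socio-demographic characteristics, including gender, ethnicity and age; indicators of addiction treatment enrollment and DTES residency"
- "a categorical variable for the number of days between government cheque issue and their study visit"

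Under Data linkages: "Participant records will be requested from hospitals, health service providers, the provincial prescription medication database", and also from police and criminal justice databases. The window is stated: "Records will be requested for a 30-month period beginning 1 year before the beginning of active study participation". The stated purposes are checking self-report, costing, and looking at service access over time.

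Under Health service utilization: "Several key secondary outcomes of the TASA study are linked to whether the study intervention can reduce or smooth health service utilization". Study design lists emergency department (ED), emergency department mental health (EDMH) and substance use hospitalization (SUH) admissions and police interactions among the pre-specified secondary outcomes. The baseline interview also asks about the past six months, including non-fatal overdose.

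**The concern.** In a trial with repeated or historical data, the participant's own earlier level of an outcome is usually a good candidate covariate. Here it is requested for every participant, and the printed list does not use it. Nothing else in the design does the same job. Randomisation is stratified by assistance type only. A person-level random effect or a dispersion parameter allows for differences between people but does not explain them by earlier use. The visit-lag covariate deals with recall and has no evident role for events counted from linked records.

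At stake is the width of the confidence intervals for the admission and police-contact rate ratios, which are among the results service providers and policy makers would look at.

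**Working it through.** **The plan's own figure.** The sample size rests on the primary binary outcome alone, and it reproduces. Reading the 20% difference as relative (0.85 against 0.68), two-sided 5% and 80% power, a two-proportion calculation gives 97 per arm.

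- The repeated-measures factor is (1 + (m − 1)ρ)/m with ρ = 0.6.
- Six cheque days: 97 × 0.667 = 64.7, so 65.
- With 33% of observations missing, 6 × 0.67 ≈ 4: 97 × 0.70 = 67.9, so 68.
- With 25% loss: 68/0.75 = 90.7, so 91; and 91 × 3 = 273.

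These figures are not in dispute. No power is stated for any secondary outcome.

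**The record window.** 12 months before + about 6 months of participation + 12 months after = 30 months, which matches the article. A prior-year count is therefore available in principle for every participant.

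**Inputs for the size of the gain.** From the article: 91 per arm, and 12 months before against 26 weeks of follow-up. Assumed, because the article gives no values: a control mean of 0.5, 1 or 2 events per 26 weeks; between-person frailty variance k = 2; a rate ratio of 0.6; complete linkage; and either half or 80% of the frailty variance persisting from the earlier year into follow-up.

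**Without the prior count (closed form, negative binomial).** SE of the log rate ratio = √[(1/μ + 1/(0.6μ) + 2k)/91], |ln 0.6| = 0.511, and power ≈ Φ(0.511/SE − 1.96).

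- μ = 0.5: √[(2 + 3.333 + 4)/91] = 0.320; Φ(−0.365) = 36%
- μ = 1: √[(1 + 1.667 + 4)/91] = 0.271; Φ(−0.07) = 47%
- μ = 2: √[(0.5 + 0.833 + 4)/91] = 0.242; Φ(0.15) = 56%

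This model never uses the prior count, so these figures cannot depend on how much variance persists.

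**With log(prior-year count + 0.5) added (simulation).** Counts were drawn from gamma frailties and analysed by negative binomial regression. The simulation was run three times, with 250, about 300 and 400 trials per scenario. Monte Carlo error in one power figure is about 3 points at 250 trials (√(0.5 × 0.5/250) = 0.032).

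| Mean per 26 weeks | Persistent share | Median SE, without to with (about 300 trials) | Power without (closed form) | Power with (range over the three runs) |
|---|---|---|---|---|
| 1 | 50% | 0.266 to 0.255 | 47% | 49–53% |
| 1 | 80% | 0.271 to 0.234 | 47% | 55–64% |
| 2 | 50% | 0.241 to 0.227 | 56% | 61–64% |
| 2 | 80% | 0.240 to 0.192 | 56% | 69–73% |

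In the 250-trial run, simulated power without the covariate was 44–50% at a mean of 1 and 50–57% at a mean of 2, in line with the closed form. At a mean of 0.5 the gain was about 2 to 8 points. The median SE fell in all six scenarios of that run, by about 3–6% with half the variance persistent and 8–20% with 80% persistent.

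**A second model as a check.** Log-normal frailties, overdispersed Poisson regression, rate ratio 0.7, frailty variance 1 or 2 and a pre/post frailty correlation of 0.5 to 0.9 gave these variance reductions for the log rate ratio: 0–11% at a mean of 0.3, 1–37% at a mean of 1 and 7–47% at a mean of 2. The direction is the same, and the size again depends on persistence.

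**The case against.** The strongest reply is that the trial calls itself exploratory, that these are secondary outcomes, and that the printed list is a common set which a statistical analysis plan could extend outcome by outcome. The visit-lag item supports that reading, since it makes little sense for linked counts. This stands in part: an unseen plan may already contain the covariate. But the article states what the multivariate analyses will adjust for, and that statement as printed leaves it out.

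Second, the gain depends on how stable a person's service use is. No section gives a distribution of admissions or police contacts, or a correlation between earlier and later use. This stands fully. That use is concentrated in a few heavy users is plausible but is an assumption. With only half the variance persistent, the gain is a few points of power.

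A reader might infer more than the document supports:

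- **That the records go unused.** Data linkages declares a use over time. Only their place in the count models is absent.
- **That the secondary outcomes are shown to be underpowered.** The article states no power for them. The general caution about insufficient power under Sample size sits with the primary calculation.
- **That overdose and violence would gain as much.** Their earlier level is a self-report, the article does not clearly assign them to a count model, and neither simulation covered them.

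**Conclusion.** The point holds as a precision improvement for secondary counts taken from linked records: ED, EDMH and SUH admissions, and police contacts if they are analysed as counts. Omitting the prior level does not bias the comparison between arms, because allocation is randomised. A reader might take chance imbalance in earlier use to invalidate the arm estimates, but it only adds to their variability, which the intervals already reflect. The primary drug-use model and the sample size are untouched.

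The gain ranges from small (rare events, or use that varies from one period to the next) to material (frequent, stable use). A clear gain needs high persistence, which the documents neither support nor refute. The priority is low: worth doing because it costs almost nothing.

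**What to change.** Add one sentence to the covariate list under Quantitative analyses: for ED, EDMH and SUH admissions and police contacts, the adjusted model also includes log(prior-year linked count + 0.5) for the same outcome. Keep the unadjusted estimates. Settle this before outcomes are compared by arm.

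Count prior events only up to the randomisation date. Follow-up assessments starts follow-up at enrolment for controls, but at the first payment on the individual schedule, after randomisation, for the intervention arms. A year counted back from the start of active participation could therefore include post-randomisation time in the intervention arms only.

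For overdose and violence, the past-six-month baseline report can be added without new data collection. That gain is unquantified and probably small if events are rare.

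Cost: no new data. The adjusted model must wait for linkage, and the plan needs a rule for participants without linked records.

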### Screening, consent and baseline assessment

Individuals expressing interest in the study are administered a brief screening questionnaire by study staff to determine whether they fulfill eligibility criteria. This includes confirmation that participants are willing and able to adhere to study procedures. Participants are required to provide proof of non-administered provincial social assistance receipt in the form of an official statement of benefits, recent bank statement, or cheque stub from a recent social assistance cash transfer. Additionally, government-issued identification is needed as verification of identity and to open a bank account at Pigeon Park Savings. Study procedures and requirements are then explained to potential participants to confirm participant interest and suitability.

During the consent process, research staff explain study procedures, potential risks and benefits of participation, planned data linkages to third party administrative data sets and other consent information outlined in the informed consent form. As is common for RCTs, after signing the consent form participants undergo a short oral “consent quiz” to ensure full comprehension of key points such as voluntary consent, randomization, confidentiality, study design and procedures, and withdrawal processes. Individuals receive additional information from study staff on any areas of misunderstanding identified by the quiz.

Following informed consent and prior to randomization, participants complete an interviewer-administered baseline assessment. This assessment includes the collection of demographic information and completion of questionnaire items to assess drug use, income generation and material security, drug-related activities and exposures, criminal activity, police contact, exposure to violence, drug debt, addiction treatment enrolment, health and social service use, cheque day activities and health related quality of life (see Measures section and Table 1). Baseline measures are collected for past 6-month as well as past 2-week time frames to ensure sufficient background information as well as data consistent with the 2-week time frame of follow-up observations.

**Table 1 Tab1:** Measures used in the TASA Trial

			Follow-up (FU) period			Post-follow-up	
Measure(s)	Screen	Baseline	FU 1-13	Intervention withdrawal	Study exit	60-day visit	Data linkage
Primary Outcome Measure							
Daily Drug Use (TLFB)		✓	✓			✓	
Demographic Measures							

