### Interventions

#### Control group

Participants randomized to this study arm receive no intervention. They continue to receive monthly social assistance payments according to the British Columbia Ministry of Social Development and Social Innovation disbursement schedule.

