#### Staggered and split and social assistance disbursement (staggered and split)

Participants in the ‘staggered and split’ intervention study arm have their social assistance payments released twice a month on days that do not fall during the week of government cheque issue. The days of income assistance receipt are spaced 2 weeks apart and determined at random. As with the staggered intervention arm, individual cheque issue days are established in relation to government cheque issue day and participants transition to their new schedule incrementally. The first individual cheque issue day falls in the week following government cheque issue, with the second occurring on the corresponding day of the week 2 weeks later. This could be, for example, Tuesday of the week following government cheque issue day and Tuesday 2 weeks after that day. This allows for five randomization possibilities for the staggered and split intervention study arm. Participants are again provided with a schedule of their individual cheque issue days for the duration of their study participation.

The change in social assistance payment schedules for both intervention arms is managed through Pigeon Park Savings, which has developed a system, in conjunction with standard social assistance direct deposit services from the British Columbia Ministry of Social Development and Social Innovation, that varies when individuals have access to their social assistance payments. Social assistance payments are directly deposited into the participant’s account, and the system “locks” their payment so that these funds cannot be withdrawn. Money is “unlocked” according to the participant’s disbursement schedule that determines both the timing and frequency at which payments are released. Intervention arm participants can develop personalized arrangements that ensure access to essential funds at specific times to prevent housing instability or payment default. A study liaison at Pigeon Park Savings manages account creation, direct deposit requests to the Ministry and the implementation of holds and releases of funds. Accounts include unlimited withdrawals and a bank card with no-fee withdrawals at credit union automated teller machines. Pigeon Park Savings banking fees are charged at a rate of $5/month, and individuals are not required to pay this fee while they are enrolled in the study.

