### Sample size

We base sample size calculations for the TASA study on an a priori minimum clinically important difference (MCID) in the rate of individuals reporting intensified drug use on government cheque issue days between control and non-control participants. For the purposes of sample size calculations, comparisons were drawn between control and staggered arm participants. We anticipate this intervention will have a lesser impact on the primary outcome of interest than the staggered and split arm and should therefore provide basis for sample size calculations. Given a lack of prior comparable experimental research, the MCID was set conservatively to a 20 % difference between control and staggered intervention arm participants. This MCID was based on results from previous observational studies that report increases in the rates of drug related harm between 24.9 and 81.2 % in the days surrounding government cheque issue [5, 7, 12, 13, 17–20, 57]. We combined this MCID with an estimate of 85 % of individuals in the control group reporting intensified substance use on community cheque issue day (*Pc*). This was set lower than 100 % to account for potential reporting biases at study screening, where all participants must indicate elevated use in order to be eligible, as well as any study participation effect on the outcome of interest among control arm participants.

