Sample size calculations used methods to detect differences between proportions in a repeated measures design and were calculated using Power and Sample Size (PASS v.12) software. Sixty-five participants per arm completing all follow-ups would allow the detection of a 20 % difference in the rates of intensified drug use between control and staggered intervention arm participants with 80 % power at a 5 % significance level. These calculations assumed that control and intervention arm rates of intensified drug use follow a Bernoulli distribution, the number of government cheque issue days falling within the observation period is 6 and, as in previous studies involving PWUD [65], the autocorrelation between measures of the same individual over time *(ρ)* is 0.6. Based on previous studies among PWUD, and noting the importance of accounting for missed follow-up visits and loss to follow-up [66], we additionally account for observation-level non-response of 33 % and a potential rate of loss to follow-up of 25 %, reaching a final sample size of 91 individuals per arm or 273 in total across all three arms. The possibility of type II, false negative findings, could result from insufficient power, or, in the event of intervention withdrawal, the dilution of the effect of the intervention in ITT analyses from participants who have resumed regular synchronized payments but are analyzed as part of the intervention arm. These risks will be partially mitigated by the inclusion of sensitivity analyses, as outlined in the Data Analysis section below.

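### The adjusted model for the primary outcome conditions on moving to Pigeon Park Savings, a step in delivering both interventions, so its arm contrast is purely randomised only if controls move too

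*Protocol article*

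**What the plan says.** The Quantitative analyses section plans mixed logistic models that give both unadjusted and adjusted odds ratios by arm, analysed by intention to treat. It does not say which of the two is primary. The adjustment set contains assistance type, socio-demographic characteristics, addiction treatment, neighbourhood residency, and two variables that are fixed after consent: "an indicator variable for whether the individual changed their financial service provider to Pigeon Park Savings (PPS) at the start of the study" and "a categorical variable for the number of days between government cheque issue and their study visit". The stated aim of the first is to remove the effect of becoming a PPS client.

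On delivery, the section on the staggered and split arm says: "The change in social assistance payment schedules for both intervention arms is managed through Pigeon Park Savings". It adds that a liaison there handles account creation and the direct-deposit requests. For the control arm the article says: "Participants randomized to this study arm receive no intervention", with payments continuing on the Ministry's schedule. Randomisation follows consent and the baseline assessment.

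Three other places bear on whether controls bank at PPS. Under Eligibility and recruitment, everyone must qualify for, and accept, becoming a client. Under Screening, everyone must show identification, in part so that an account can be opened. Under Data linkages, credit-union records are to be requested for all participants.

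**The concern.** An intervention participant who banks elsewhere has to move to PPS for the payment lock to work. For that person the move is part of receiving the treatment. A control has no such need. The switch indicator may therefore be partly or wholly a consequence of allocation, and adjusting for it removes some of the protection that randomisation gives.

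In the extreme case, where no control switches, the effect of switching is estimated only within the intervention arms. The adjusted arm coefficient then sets participants who were already PPS clients in the intervention arms against all controls, clients or not. Anything that distinguishes long-standing clients enters that contrast.

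The indicator also sits badly with intention to treat. An intervention participant who never moves to PPS gets the same code as someone who was already a client.

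**Working it through.** **Inputs from the Sample size section.** The control rate comes from "an estimate of 85 % of individuals in the control group reporting intensified substance use". The effect comes from "the MCID was set conservatively to a 20 % difference between control and staggered intervention arm participants". The error rates come from "with 80 % power at a 5 % significance level", taken here as two-sided. The section also gives six cheque days per person, a within-person correlation of 0.6, 65 completers per arm, 33% missed observations and 25% loss to follow-up.

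**The plan's own figure.** Reading the 20% as relative, the staggered rate is 0.85 × 0.80 = 0.68. Two independent proportions then need 97 per arm. The repeated-measures factor is (1 + 5 × 0.6)/6 = 0.667, and 97 × 0.667 = 64.7, so 65. Losing a third of the observations leaves four per person, with factor (1 + 3 × 0.6)/4 = 0.70, and 65 × 0.70/0.667 = 68.25. Dividing by 0.75 gives 91 per arm, or 273 in total. All the stated figures reproduce. The corresponding odds ratio is (0.68/0.32)/(0.85/0.15) = 0.375.

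**Assumptions that the article does not supply.** f is the share of participants who are already PPS clients. c is the share of non-client controls who move to PPS.

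**Precision when c = 0 (linear approximation).** Let n be the number per arm. The arm contrast equals the difference in arm means minus (1 − f) times the switch coefficient.
- Two-arm model: the switch coefficient has variance σ²/[n f(1 − f)]. The contrast has variance (σ²/n)[2 + (1 − f)/f], so the ratio to the unadjusted variance is R = 1 + (1 − f)/(2f) = (1 + 1/f)/2.
- One pooled three-arm model: both intervention arms inform the switch coefficient, so its variance halves and R = 1 + (1 − f)/(4f).
- Power is Φ(2.80/√R − 1.96), where 2.80 = 1.96 + 0.84.

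| f | R, three-arm | Power | R, two-arm | Power |
|---|---|---|---|---|
| 0.5 | 1.25 | 71% | 1.5 | 63% |
| 0.3 | 1.58 | 60% | 2.2 | 48% |
| 0.2 | 2.0 | 51% | 3.0 | 37% |

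The comparison of the two intervention arms with each other is not inflated (R = 1), because the expected switch share is the same in both.

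**Precision when controls switch.** In the two-arm model with c = 0.5, the inflation is 1.03 to 1.30 and power 79% to 69%, for f from 0.7 down to 0.1. With c = 1 the inflation is 1.00 and power stays at 80%.

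**Bias.** This was checked by large-sample logistic simulation of control against staggered. The true odds ratio was 0.375, switching had no effect of its own, and existing clients differed from non-clients by ±0.5 on the log-odds scale (an assumption).
- c = 0: the adjusted odds ratio runs from about 0.26 to 0.56 at f = 0.2, and from 0.30 to 0.49 at f = 0.5.
- c = 0.5: it runs from about 0.33 to 0.42 at f = 0.2, and from 0.34 to 0.42 at f = 0.5.
- c = 1, or clients who do not differ in risk: no bias.
- The unadjusted odds ratio stayed at 0.37 to 0.38 throughout.

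**The case against.** The strongest reply is that controls may well open PPS accounts. Everyone must be willing to be a client, and identification for an account is asked for before allocation is known. One secondary outcome is the time that a participant's bank account holds little or no money. The only banking source listed is the partner credit union, with records sought for all participants, so comparing arms on that outcome would need controls to hold accounts there. If every non-client control moves, the indicator merely marks who was not a client before, and it does no harm. This stands as far as it goes. A reader might infer that the indicator is zero in controls, but the article does not establish that. Nor does it state that controls switch: willingness at screening is not a transfer of banking.

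The second reply is that the unadjusted odds ratio is also planned and is free of the problem. That is correct. A reader might infer that the primary analysis itself is biased, but the article does not call the adjusted model primary. What remains open is which estimate governs if the two disagree.

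Two further inferences are tempting and not supported.
- **Visit lag.** The visit clock does start differently by arm: at enrolment for controls, and at the first payment on the individual schedule for the others. With visits simulated every 14 days on an assumed 28/28/35-day cheque cycle, the lags differ in the first cycle but even out over six, and the variance inflation is about 1.00. Bias would need attendance timing to depend on both arm and drug use, which the article does not show.
- **Baseline drug use.** "Daily Drug Use (TLFB" is recorded at baseline in Table 1 but is not a covariate. Leaving it out does not bias a randomised contrast. The efficiency gain is unknown, because the outcome is a within-person relative increase and a two-week baseline window may miss cheque day.

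**Conclusion.** The concern holds in a conditional form. The adjusted model includes a variable that delivery of both interventions can set, and the article does not secure equal switching in controls. The harm depends on f and c, neither of which is given. With no control switching and f between 0.2 and 0.5, power for an intervention arm against control falls from 80% to between 51% and 71% in a pooled three-arm model, or to between 37% and 63% in a two-arm model. The direction of any bias cannot be stated, and there is none if existing clients carry the same risk and switching has no effect of its own. If all non-client controls also switch, nothing is lost. The unadjusted intention-to-treat odds ratio is sound in every scenario.

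**What to change.** 1. Replace the switch indicator with PPS client status before randomisation (yes or no), defined identically in all three arms. The baseline banking-practices item in Table 1 can supply it, or the credit-union records, which reach back one year before active participation.
2. Move the model that adjusts for the switch to a sensitivity analysis, labelled as conditioning on a step that follows allocation.
3. Name as primary an estimate that does not condition on the switch.
4. State whether controls open PPS accounts, and report by arm how many participants were already clients and how many moved.
5. Visit lag can stay as a recall sensitivity adjustment. Baseline drug use may be added for efficiency, but it is optional.

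The cost is a change of analysis wording, with no new data collection. If all participants do open accounts, the replacement variable carries the same information as the present one, so the change is safe under either reading.
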